#### Blood and saliva sampling

All blood samples will be obtained from a forearm vein using venepuncture technique with participants in an overnight (> 10 h) fasted state. Samples will be collected into vacuumed EDTA, lithium heparin and serum separator tubes, centrifuged at 3000 × g for 10 min at 4 °C and aliquoted as plasma (EDTA) or serum across five 1.0 mL Cryovial tubes and stored at −80 °C until analysis of deuterium enrichment, amino acid concentration, insulin concentration and urea concentration. Saliva samples will be collected on multiple for the assessment of total body water enrichment. The measurement of total body enrichment is required to determine the deuterium in the body for the calculation of Myo-MPS. Participants will collect a 2-mL saliva sample in a designated vial using the passive drool technique before initial storage in the fridge (at home) and subsequent transfer to −80 °C freezer in the laboratory until subsequent analysis.

#### Body composition

Body mass will be assessed to the nearest 0.1 kg using digital scales (TFW150, Adam Equipment, Milton Keynes, England) with participants wearing identical light clothing at baseline, post prehabilitation and post immobilisation laboratory visits. At baseline, skinfold measurements of body fat percentage will be conducted in duplicate across eight body sites (triceps, biceps, subscapular, iliac crest, supraspinal, abdominal, thigh and calf) by a trained ISAK practitioner using Harpenden callipers (HaB, UK). Body fat will be estimated using the anthropometric equation presented by Eston et al. [13]. Leg lean mass (immobilised and non-immobilised legs) will be measured at baseline, after the 1 week prehabilitation period and after the 5 day prehabilitation period using dual energy x-ray absorptiometry (DXA, Hologic Horizon W scanner). Ultrasound will be used to assess muscle thickness of the *rectus femoris* for both the immobilised and non-immobilised legs at the same time points. For this assessment, leg length from the hip crease to the top of the patella will be measured with the participant seated on a plinth with their legs straight out in front of them. Once this distance has been obtained, 1/3rd of the distance from the patella will be marked on the thigh. A linear ultrasound probe coated in imaging gel will be placed at this position and the *rectus femoris* located. Once located, an image will be taken with the thickest section of this muscle in the centre, from which muscle thickness will be measured.

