## Background

The term *muscle disuse* refers to a scenario in which a muscle group(s) is unloaded over an extended (> 2 days) time period, e.g. limb immobilisation due to injury or following surgery. A period of limb immobilisation-induced muscle disuse is widely established to cause muscle atrophy [8]. In this regard, only 5 days of leg immobilisation was sufficient to elicit a physiologically relevant (3.5%) decline in quadriceps muscle CSA [32]. At the metabolic level, this muscle atrophy is primarily mediated by a decreased response of muscle protein synthesis (MPS) rather than increased stimulation of muscle protein breakdown [24]. Accordingly, a study by the same group demonstrated an ~ 30% decline in response of MPS to protein ingestion after 14 days in a leg brace, indicating that immobilisation led to a state of muscle anabolic resistance [33]. These findings highlight the importance of targeted, non-pharmacological, interventions to attenuate the immobilisation-induced decline in MPS in order to maintain muscle mass during unplanned (i.e. injury) or planned (i.e. surgery) periods of disuse.

Resistance exercise training serves as the most potent non-pharmacological stimulus of MPS [4]. Moreover, the provision of dietary amino acids in combination with resistance exercise exhibits an additive effect, stimulating MPS to a greater degree than exercise alone [5]. Multiple clinical trials have investigated the efficacy of a nutritional intervention to mitigate the suppressed response of MPS during a period of immobilisation [34], However, to our knowledge, no studies to date have investigated the impact of a combined nutritional and exercise prehabilitation programme, implemented prior to a period of immobilisation, on mitigating the disuse-induced decline in MPS and muscle mass. To fill this gap in knowledge, we will conduct a placebo-controlled clinical trial that combines β-lactoglobulin supplementation as a novel milk protein with resistance exercise training and measure integrated free-living rates of MPS before and after 5 days of limb immobilisation. The placebo group will be an energy-matched carbohydrate (dextrose) control.

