#### Power calculation

The sample size for this study has been estimated using an a priori power analysis of a previously published study by Kilroe et al. [19] that utilised the same unilateral leg immobilisation protocol, primary endpoint measurement (free-living integrated MPS rates assessed by deuterium oxide tracer methodology) and participant characteristics (healthy young adults). We calculated an effect size (d) of 1.6 for the primary endpoint (MPS) using Eq. 1.1$$\mathbf d\boldsymbol=\boldsymbol(\mathbf\mu\mathbf1\boldsymbol-\mathbf\mu\mathbf2\boldsymbol)\boldsymbol/\mathbf{SD}$$where μ1 is the mean value for muscle protein synthesis in group 1, μ2 is the mean value for muscle protein synthesis in group 2 and SD is the pooled standard deviation.

This effect size was entered into G*Power (version 3.1.9.2), with power set to 0.8 and significance level (*α*) set to 0.05. The required sample size was projected to be 12 per group, for a total of 24 participants. Hence, we plan to recruit 24 healthy, young (18–45 years) males and females from the local area. Recruitment will proceed on a rolling basis until the adequate sample size is reached. Emphasis will be placed on considering the demands of the study before enrolment to minimise loss to follow-up.

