#### Isokinetic dynamometry

For isokinetic dynamometry, participants will be seated on a Kin-Com (Chattangooga Group) so that their knee is ~ 2 cm away from the edge of the seat and their back is upright and supported by the backrest. Straps will be placed across their chest and waist to isolate movement to the leg only. The lever arm will be positioned to align with the centre of rotation of the knee, and the ankle strapped on to the lever arm ~ 3 cm proximal to the ankle joint. The length from the centre of rotation of the lever arm to the attachment point at the ankle will be noted. Participants will then be asked to perform three single leg maximal contractions at 60°/second, moving their leg from a 90° angle to straight and back again. Participants will be asked to perform three more maximal contractions at 120°/s. Finally, participants will be asked to perform three maximal isometric contractions, with their leg fixed at a 90° angle and the twitch interpolation protocol described above will be applied. Isokinetic dynamometry will be conducted on both the immobilised and non-immobilised legs separately.

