### Statistical analysis strategy

All statistical analyses will be performed using IBM SPSS Statistics for Windows, v.22.0 (IBM, Armonk, NY, USA). Data will be checked for normal distribution using the Shapiro-Wilk test. The primary endpoint measurement is myo-MPS. Secondary endpoints are leg lean mass (DXA), *rectus femoris* muscle thickness (ultrasound), muscle fibre CSA (immunohistochemistry) and quadriceps muscle strength (isokinetic dynamometry). All measurements will be analysed using a 2-way between and within mixed model ANCOVA with condition (ß-lactoglobulin vs. placebo) as the between-group factor and time period (basal *vs*. prehabilitation *vs.* immobilisation) as within-group factors. Diet and physical activity status will be input as covariates. Where appropriate (i.e. measurements of MPS, leg lean mass, muscle thickness and quadriceps muscle strength), a within-subject control (non-immobilised leg) will be applied to the statistical model when making between group comparisons. The key objective is to compare the effect of the intervention vs. placebo in an unpaired sample. We plan to make three comparisons between the two groups (Δ baseline to immobilisation, Δ prehabilitation to immobilisation, and Δ baseline to prehabilitation for all measurements), disregarding sex as a factor. There is a risk this may introduce type 2 error (rather than type 1 because the randomisation is granular), but we have no reason to anticipate that sex will be a significant confounder. Additional justification for this strategy is because we anticipate that the number of male and female participants will not be equal. The strategy will be to determine from the ANCOVA above whether the intervention is a significant source of variance for each of the primary and secondary endpoint measurements. Bonferroni post hoc testing will be undertaken only if *F* is significant (*P* < 0.05), and there is no variance in homogeneity. The post hoc test will be a *t* test but with an adjustment in the *P* value to accommodate the number of comparisons. The adjustment will be to add a degree of freedom for each of the comparisons. We consider this statistical approach optimal for permitting reliable discovery in a reasonable timeline. Statistical significance will be set an *α*-level of *P* < 0.05.

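### Muscle thickness is read from one ultrasound image per leg per visit, with no repeatability figure, for an expected 5-day change of 3.5% or less; averaging three re-placed images would buy precision cheaply

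*Protocol article*

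**What the plan says.** The Body composition section of the protocol article describes the scan in order. Leg length is measured from hip crease to patella, and then "1/3rd of the distance from the patella will be marked on the thigh". The probe is put there and the rectus femoris is found. The last step is: "Once located, an image will be taken with the thickest section of this muscle in the centre, from which muscle thickness will be measured". This is done "for both the immobilised and non-immobilised legs at the same time points" as DXA, that is, at baseline, after prehabilitation and after immobilisation.

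The Statistical analysis strategy section lists the secondary endpoints as leg lean mass and then "muscle thickness (ultrasound), muscle fibre CSA (immunohistochemistry) and quadriceps muscle strength (isokinetic dynamometry". It plans three between-group comparisons, all of changes between periods, and applies the non-immobilised leg as a within-subject control for thickness among other measures.

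Replication is stated elsewhere. In the same section, "skinfold measurements of body fat percentage will be conducted in duplicate across eight body sites"; under Isokinetic dynamometry there are "three single leg maximal contractions at 60°/second", and three contractions again for the other strength tests.

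On the size of change to expect, the Background says that "only 5 days of leg immobilisation was sufficient to elicit a physiologically relevant (3.5%) decline in quadriceps muscle CSA". The article gives no figure for rectus femoris thickness and none for the repeatability of the ultrasound reading.

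**The concern.** A single reading from a hand-placed probe carries the whole of that day's placement and reading error, and a change score carries it twice. The signal is small: a few per cent at most over five days. The effect being sought, attenuation of that loss by the supplement, can be no larger than the loss if it works by preventing it, and is probably a fraction of it.

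If the error of a single reading is of the same order, the between-arm comparison of thickness, with 12 per arm, could miss a real effect for a reason that is easily avoided. The baseline-only, descriptive skinfolds are taken in duplicate, so replication was considered in this section but not applied to a measure followed over time.

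**Working it through.** **Inputs from the protocol article**
- One image per leg per visit (Body composition).
- Change scores compared between arms (Statistical analysis strategy).
- 12 per group (Power calculation).
- 3.5% fall in quadriceps CSA after 5 days (Background).

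**The plan's own figure.** There is none for thickness. The sample size rests on MPS: "We calculated an effect size (d) of 1.6 for the primary endpoint (MPS". With power 0.8 and a two-sided α of 0.05, a two-sample t test needs 7.23, so 8 per group rather than the stated 12. That is a separate matter. It says nothing about thickness, and 12 per arm is taken here as given.

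**Assumption.** The between-visit CV of a single image is not in the article. I show 1%, 2%, 3% and 5%.

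**Step 1: expected change in thickness.** Area has two dimensions and thickness one.
- All of the CSA loss in thickness: 3.5%.
- Equal shrinkage in both dimensions: 1 − √(1 − 0.035) = 1.77%.

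**Step 2: error SD of one participant's change.** With k independent images averaged per visit, SD = √2 × CV / √k. Three images in place of one multiply it by 1/√3 = 0.577, a cut of 42%.

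**Step 3: measurement-error part of the SE of the between-arm difference.** SE = SD × √(2/12).

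**Step 4: power.** Two-sample t test, 12 per arm, two-sided α 0.05, measurement error as the only variance, to detect a halving of a 3.5% loss (a difference of 1.75 points).

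| CV | Change SD in points, 1 image / mean of 3 | SD with 1 image ÷ 3.5% | SD with 1 image ÷ 1.77% | SE of difference, 1 / 3 | Power, 1 / 3 |
|---|---|---|---|---|---|
| 1% | 1.41 / 0.82 | 0.40 | 0.80 | 0.58 / 0.33 | 0.83 / about 1.0 |
| 2% | 2.83 / 1.63 | 0.81 | 1.60 | 1.15 / 0.67 | 0.31 / 0.71 |
| 3% | 4.24 / 2.45 | 1.21 | 2.40 | 1.73 / 1.00 | 0.16 / 0.39 |
| 5% | 7.07 / 4.08 | 2.02 | 4.00 | 2.89 / 1.67 | 0.09 / 0.17 |

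**Step 5: where error equals change, with one image.** CV = 3.5/√2 = 2.47% for a 3.5% change, and 1.77/√2 = 1.25% for a 1.77% change.

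**Step 6: sensitivity.**
- Complete prevention of a 3.5% loss: power is 0.83 with one image at CV 2%, 0.64 at CV 2.5% and 0.49 at CV 3%. With three images at CV 3% it is 0.92.
- If the control leg is used as a simple difference, a second leg's error enters and the SD grows by √2. At CV 2%, power for halving a 3.5% loss is then 0.18 with one image and 0.43 with three.
- If a share s of the error variance is common to all images at a visit, averaging three multiplies the SD by √(s + (1 − s)/3). That is 0.577 at s = 0, √0.667 = 0.816 (an 18% cut) at an illustrative s = 0.5, and 1 (no gain) at s = 1.

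These powers leave out true between-person variation in change, which would lower all of them and narrow the relative gain from averaging.

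**The case against.** The best reply is that a journal article condenses the protocol, and that the number of frames is an operating detail for the fuller document. That carries some weight, but the article describes this scan step by step and states replication for skinfolds a few lines earlier. A single reading is the fair reading of the text.

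The second reply is that the size of the problem rests on a CV that the article does not give. That stands. At CV 1%, one image already gives power 0.83 for halving a 3.5% loss, so the argument must stay conditional. The comparator is also indirect: quadriceps CSA, not rectus femoris thickness.

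Third, averaging deals only with error that is independent between images. Error from a visit-wide shift of site stays, which is why the site has to be fixed as well.

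Fourth, the stakes are limited. Thickness is one of four secondary endpoints, it is not named in the numbered objectives at the end of the Background, and DXA and fibre CSA also address muscle size. That is fair, and it bounds the importance of the point.

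A reader might also infer three things that the text does not support:
- That the site is found afresh at each visit by a free search for the thickest part. The article marks a fixed one-third level and does not say whether the mark is kept or renewed. The thickest-section wording reads as a centring rule at that level.
- That thickness is the one endpoint left unreplicated. No repeat DXA scan is described either, and three maximal contractions may be attempts at a maximum rather than readings to be averaged.
- That the error could imitate a treatment effect. With blinded allocation, random reading error adds variance; it does not push the arms apart systematically.

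**Conclusion.** The point holds as a matter of precision. The article specifies one image per leg per visit for a secondary endpoint analysed as change, where the expected 5-day change is about 1.8% to 3.5%. It is tempting to say outright that the error is as large as the change. The article does not support that, because it reports no repeatability. The supported statement is conditional: at a between-visit CV of about 1.25% to 2.5% the error SD of one participant's change equals the expected change, below that range it is smaller and above it larger.

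Nor does parity at the level of one participant make the endpoint useless, because the trial compares means of 12. At CV 2.5%, the measurement-error part of the SE is 1.44 points, and power for complete prevention of a 3.5% loss is 0.64 on measurement error alone. The consequence is lost precision without bias. The gain available from averaging three images is at most a 42% cut in the measurement-error SD, and less to the extent that error is shared within a visit. The primary endpoint and the sample size are untouched.

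**What to change.** In the Body composition section, replace the single image with three images per leg per visit at the marked one-third level. Lift and re-place the probe each time, keep the rule of centring on the thickest section, and use the mean thickness as the endpoint value. Record the baseline distance from the patella for each leg and reuse it at the two later visits, so that the level does not depend on measuring leg length again.

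The cost is a few more minutes per visit and three times as many images to read, with the same operator, probe and session. No extra visit, staff or invasive procedure is needed. The three images would also let the trial report a within-visit repeatability figure, which the article now lacks. The change will not reduce error shared by all images at a visit, or true differences between participants.

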#### Isokinetic dynamometry

For isokinetic dynamometry, participants will be seated on a Kin-Com (Chattangooga Group) so that their knee is ~ 2 cm away from the edge of the seat and their back is upright and supported by the backrest. Straps will be placed across their chest and waist to isolate movement to the leg only. The lever arm will be positioned to align with the centre of rotation of the knee, and the ankle strapped on to the lever arm ~ 3 cm proximal to the ankle joint. The length from the centre of rotation of the lever arm to the attachment point at the ankle will be noted. Participants will then be asked to perform three single leg maximal contractions at 60°/second, moving their leg from a 90° angle to straight and back again. Participants will be asked to perform three more maximal contractions at 120°/s. Finally, participants will be asked to perform three maximal isometric contractions, with their leg fixed at a 90° angle and the twitch interpolation protocol described above will be applied. Isokinetic dynamometry will be conducted on both the immobilised and non-immobilised legs separately.

#### Diet and physical activity tracking

To assess physical activity patterns, participants will complete a three-day physical activity questionnaire and wear an Actigraph GT9X monitor (ActiGraph, Pensacola, FL, USA) for four consecutive days. These two activity monitoring techniques require participants to include two weekdays and one weekend day. This assessment will be conducted at three different time points throughout the study, once at baseline, once during the resistance exercise training period and once during the immobilisation period, in order to track changes in physical activity at different phases of the study.

The Actigraph will be secured in a pouch and worn on whichever ankle will not be immobilised. Participants will be instructed to remove the monitor during bathing, swimming, and sleeping activities but to wear it at all other times. The monitor records acceleration in three dimensions, and data will be presented as both mean vector magnitude counts per minute (VM) and time spent performing different activity levels. The threshold for these activity levels is based on a validation study for moderate and vigorous activities with this specific monitor [26], in combination with the Actigraph recommended cut point for sedentary activity [14]. Based on these studies, the cut points for sedentary, light, moderate and vigorous activity levels are < 100, 100–10,431, 10,432–19,813, and > 18,914 VM, respectively.

The physical activity questionnaire was selected from Bouchard et al. [7] as a 3-day questionnaire validated in a general population. In brief, the questionnaire requires participants to qualify the type of activity performed during each 15-min period for 72 h on a scale from 1 to 9. The scale will be discussed with participants before they are given the questionnaire. If a participant is uncertain about a particular activity, this will be discussed with a researcher to come to an agreement about the rating. The corresponding energy cost of each category was also taken from Bouchard et al. [7] and will be used to calculate total energy expenditure in METS for the three consecutive days. Dietary energy and macronutrient intake will not be strictly controlled during the trial but will be monitored by the research team to ensure background protein intake does not surpass 1.2 g•kg body mass^−1^•day^−1^.

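### The moderate and vigorous accelerometer cut points overlap from 18,915 to 19,813 VM, so the split of time between those two levels is not uniquely defined there

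*Protocol article*

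**What the plan says.** The Protocol article, under Diet and physical activity tracking, has participants wear an ankle accelerometer for four consecutive days at three points: baseline, the training period and the immobilisation period. On outputs it states that "data will be presented as both mean vector magnitude counts per minute (VM) and time spent performing different activity levels". The second of those outputs needs cut points. The sedentary band is below 100 and the light band is 100 to 10,431; the moderate and vigorous bands follow as "10,432–19,813, and > 18,914 VM, respectively".

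On their origin, the section says: "The threshold for these activity levels is based on a validation study for moderate and vigorous activities with this specific monitor". The sedentary limit comes from the manufacturer's recommendation.

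The same section describes a second, separate activity measure. This is a three-day questionnaire whose category energy costs "will be used to calculate total energy expenditure in METS for the three consecutive days".

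Under Statistical analysis strategy, the only mention of activity is "Diet and physical activity status will be input as covariates". The measure meant is not named. Activity is not among the primary or secondary endpoints listed there.

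**The concern.** Activity levels used to divide up wear time should be mutually exclusive: each minute belongs to one level. The printed moderate band runs up to 19,813, while the vigorous band already starts just above 18,914. The two rules contradict each other between those figures.

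This is a fixed operational definition that produces a reported output, not background text. Someone scoring the files from the article must either count the overlapping minutes in both levels or choose an order of precedence that the article does not give. Two analysts could follow the text faithfully and report different moderate and vigorous times from the same recording. The trial recruits physically active adults, and Table 1 accepts vigorous activity as one way to qualify, so minutes at high intensity are plausible, at least at baseline.

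**Working it through.** **Inputs** (all from Diet and physical activity tracking, in VM):

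- sedentary: below 100
- light: 100 to 10,431
- moderate: 10,432 to 19,813
- vigorous: above 18,914

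**Step 1: the boundaries in turn**, for whole-number values.

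- Sedentary/light: the last sedentary value is 99 and the first light value is 100. No gap, no overlap.
- Light/moderate: 10,431 is followed by 10,432. No gap, no overlap.
- Moderate/vigorous: the last moderate value is 19,813 and the first vigorous value is 18,915. Overlap.

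**Step 2: size of the overlap.**

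- Values meeting both rules: 19,813 − 18,915 + 1 = 899.
- Width of the moderate band as printed: 19,813 − 10,432 + 1 = 9,382.
- Share: 899 / 9,382 = 9.6%.
- If the moderate upper bound is the wrong figure and should be 18,914, the width is 18,914 − 10,432 + 1 = 8,483 and the share is 899 / 8,483 = 10.6%.

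These are shares of a range of counts. They are not shares of participants' minutes, for which the document gives no figures.

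**Step 3: which repairs close the boundary.**

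| Moderate | Vigorous | Overlap | Unclassified value |
|---|---|---|---|
| 10,432–18,914 | > 18,914 | 0 | none |
| 10,432–19,813 | > 19,813 | 0 | none |
| 10,432–18,913 | > 18,914 | 0 | 18,914 |
| 10,432–19,813 | > 19,814 | 0 | 19,814 |

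The last two rows are what results from undoing a digit swap (8 and 9) in one bound and leaving the inequality alone. Each leaves one value in no band, so the inequality has to be checked along with the number. The document does not show which repair is right.

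**Step 4: which outputs depend on this boundary.**

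| Output | Uses the moderate/vigorous boundary? |
|---|---|
| Mean VM | No |
| Sedentary time, light time | No |
| Moderate and vigorous time combined, taken as all time at or above 10,432 VM | No |
| Questionnaire energy expenditure | No |
| Moderate time and vigorous time reported separately | Yes |
| Activity covariate | Only if built from the separate moderate or vigorous minutes; the article does not say |
| Primary and secondary endpoints as measured | No |

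**The case against.** The strongest reply is that this is a slip in print. The two figures look like a transposition: swapping the 8 and 9 in either one brings it next to the other (18,913 and 18,914, or 19,813 and 19,814). The thresholds are attributed to a cited validation study, so the intended figure can be recovered, and nothing shows that recordings will be scored with the misprinted pair. This is probably the right explanation and it keeps the matter small. It does not remove the point, because the article gives no way to tell which figure is correct and no other section corrects it.

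A reader might infer three stronger things, none of which the document supports.

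- **That the activity data as a whole are wrong.** Only the separation of moderate from vigorous time is affected, and only between 18,915 and 19,813 VM.
- **That minutes will be counted twice, so that level times exceed wear time.** This would follow if the software applied both printed rules independently. The article does not describe the software settings, so it is a possibility and not a finding.
- **That the error enters every model through the covariate.** The analysis section names no activity measure. Mean VM and questionnaire energy expenditure are both candidates, and neither uses the cut points.

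It is also fair to object that the 9.6% does not measure impact. It describes the width of the contradiction, and its denominator uses a bound that may itself be wrong.

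**Conclusion.** The inconsistency is certain on the printed text: 899 whole-number values satisfy two definitions meant to be exclusive. At least one bound, or its inequality, must change. The conclusion assumes only that the four levels were intended not to overlap, which the two clean boundaries and the reporting of time per level both imply.

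The consequence is limited. Separate moderate and vigorous times are ambiguous in that range, by an amount that cannot be derived from the document. An effect on the models is conditional on an unstated choice of covariate, and no effect on the primary or any secondary endpoint is shown. Severity is minor.

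**What to change.** Check the moderate upper bound and the vigorous lower bound against the cited validation study. Print one shared boundary, with inequalities that match, so that the bands meet with no overlap and no unclassified value. Before any activity-level times are derived, confirm that the scoring software holds the same figures.

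The cost is one corrected line in the protocol and one check of the software settings. If recordings have already been scored, look at which boundary was used and re-score only if it differs from the verified one. The overlap does not by itself call for a different activity covariate.
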